**Assessment of causality**

All SAEs within the first 28 days post-administration of ciprofloxacin will be assessed for a causal relationship with ciprofloxacin by the Principal Investigator / designee. Every effort will be made by the study team to explain each event and assess its causal relationship, if any, to administration of ciprofloxacin. Appropriate medical judgment will be used to determine the causal relationship, considering all relevant factors including the pattern of reaction, temporal relationship, re-challenge, biological plausibility, and confounding factors such as concomitant medication, concomitant disease and relevant history.

The likelihood of the relationship of the event to ciprofloxacin will be recorded as follows:

**Related,** when there is a reasonable possibility that ciprofloxacin contributed to the event.

**Unrelated,** when administration of ciprofloxacin is not suspected to have contributed to the event (CIOMS, 2003).

All post-administration serious adverse events (e.g. those occurring within 30 minutes of administration) will be considered related to ciprofloxacin.

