**SAFETY**

**Documenting serious adverse events**

Passive surveillance for serious adverse events will be conducted from study beginning through 28 days following the last dose of ciprofloxacin administered (whether in the household-level or community-level prophylaxis arm). This surveillance will cover all study participants and be carried out at the health facility-level by study staff.

Serious adverse events (SAEs) are defined as any untoward medical occurrence that at any dose of medicine received results in death, is life threatening, requires inpatient hospitalization or prolongation of existing hospitalization, or results in persistent or significant disability or incapacity, or any medically important event / reaction that may jeopardize the subject and may require medical or surgical intervention to prevent one of the outcomes listed above (Bonhoeffer 2002 and 2004).

SAEs will be defined as an adverse event that at any dose of ciprofloxacin that

1. results in death;
2. is life threatening;
3. requires inpatient hospitalization or prolongation of existing hospitalization;
4. results in persistent or significant disability or incapacity
5. results in congenital malformation or birth defect
6. is medically important event / reaction that may jeopardize the subject and may require medical or surgical intervention to prevent one of the outcomes listed above

Persons who die in a health facility will have events before and at the time of death transcribed from hospital records to determine the cause of death. If death occurs outside of the hospital, cause of death will be established using a standard verbal autopsy form administered to determine the clinical picture and treatment received before death.

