**Definition of research subject and identification of gatekeepers**

Given that the primary outcome of interest is the overall meningitis incidence in the three different arms, all residents of randomized villages should be considered research subjects (Weijer, 2012; van der Graaf, 2015). Although there are certain unknowns regarding the sample size necessary for the evaluation of the primary outcome (see section “Sample Size” above), even when using conservative estimates, we could reasonably expect at least 20 000 persons to be living in the study area of each arm, therefore a total of at least 60 000 research subjects under the current definition.

The logical “gatekeepers” as described by the Ottawa Statement for the proposed trial are the health and political/administrative leaders of the study areas in question. For the purposes of this study, the gatekeepers who will be asked for permission will be the doctor or nurse in charge of the Health Center in a given HA, as well as the village chief and his/her deputies for the villages eligible for inclusion.

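### The rule deeming post-dose SAEs related conflicts with the 28-day causality assessment, and an SAE list tied to a ciprofloxacin dose leaves serious events without a standard-care comparator

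*Combined protocol and SAP*

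**What the plan says.** All of this is in the Combined protocol and SAP, mainly in the Safety chapter.

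*Assessment of causality* sets the general rule: "All SAEs within the first 28 days post-administration of ciprofloxacin will be assessed for a causal relationship with ciprofloxacin". Medical judgment is to be used, with confounding factors considered, and the result is recorded as related or unrelated. The section closes with a second rule: "All post-administration serious adverse events (e.g. those occurring within 30 minutes of administration) will be considered related to ciprofloxacin".

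*Documenting serious adverse events* fixes who is watched and for how long. The period is set by: "Passive surveillance for serious adverse events will be conducted from study beginning through 28 days following the last dose of ciprofloxacin administered". The population is set by: "This surveillance will cover all study participants and be carried out at the health facility-level by study staff". *Definition of research subject and identification of gatekeepers* takes the widest view of that population: "all residents of randomized villages should be considered research subjects". Standard-care villages are therefore included.

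The same safety section defines an SAE twice. The first definition speaks of "any untoward medical occurrence that at any dose of medicine received results in death, is life threatening", followed by the other usual criteria. The second is a six-item list that opens: "SAEs will be defined as an adverse event that at any dose of ciprofloxacin that". Neither mentions meningitis, although elsewhere "the primary outcome of interest is the overall meningitis incidence in the three different arms".

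**The concern.** Two pairs of rules do not fit together.

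The first pair concerns causality. One sentence asks for a judgment on each event; another decides the answer for a class of events whose boundary is given only by example. Staff who follow the text could classify the same late event either way.

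The second pair concerns population and definition. The plan watches all arms but gives an operative list that only a ciprofloxacin recipient can satisfy. The trial has a randomized standard-care arm under the same facility surveillance, yet serious events there have no place in the count. *Summary of known and potential risks* states that there are no data on ciprofloxacin used this way in the meningitis belt, and children and pregnant women are eligible for dosing, so a by-arm count of serious events would be worth having.

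A smaller matter follows. A meningitis case in a recipient that is fatal, life-threatening or leads to admission is both a primary-outcome event and an SAE, and no rule says how to handle the overlap.

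**Working it through.** There is no sample size, power or event figure in the plan to reproduce on this point. The check is mainly textual, with one calculation for scale.

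**1. Causality.**
- Rule A: every SAE within 28 days of a dose is assessed and may be called unrelated.
- Rule B: SAEs after administration are deemed related. The 30-minute period is introduced as an example and sets no boundary.
- On the literal reading, every event under Rule A also falls under Rule B, and nothing can be unrelated. The adjudication in *Documenting serious adverse events* (Principal Investigator and Study Monitor, with a third party if they disagree) would have nothing to decide.
- On the narrow reading, Rule B covers only immediate events and the two rules are compatible. The text does not say this.
- Two other details suggest incomplete adaptation. Onset is to be recorded relative to vaccination, although the intervention is an antibiotic. Causality is given to the Principal Investigator and Study Monitor in one section and to the Principal Investigator or a designee in the next.

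**2. Definition against population.**

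| Person under surveillance | First definition (dose of a medicine) | Six-item list (dose of ciprofloxacin) |
| --- | --- | --- |
| Ciprofloxacin recipient | can have an SAE | can have an SAE |
| Non-recipient in a ciprofloxacin arm | only if some medicine was taken | cannot |
| Standard-care resident | only if some medicine was taken | cannot |

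The definitions disagree in the last two rows, and neither covers a person who took no medicine. *Data analysis* plans no by-arm safety tabulation that would settle the matter.

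**3. Endpoint overlap.** The list has no exemption for meningitis. Cases meeting a seriousness criterion after a dose qualify; others do not.

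**4. Scale, from the protocol's own figures.**
- Inputs: 20 000 residents per arm (*Definition of research subject*); 1% standard-care attack rate and 70% reduction (the example under Table 2); case fatality of 6.8% and 10.5% (*Emergence of NmC*).
- Cases = residents × attack rate × (1 − reduction). Deaths = cases × case fatality.
- Standard care: 20 000 × 0.01 = 200 cases; 200 × 0.068 = 13.6 and 200 × 0.105 = 21.0, so about 14–21 deaths.
- A ciprofloxacin arm: 200 × 0.30 = 60 cases; 60 × 0.068 = 4.1 and 60 × 0.105 = 6.3, so about 4–6 deaths.
- Range for a ciprofloxacin arm, with attack rates of 0.5–2% and reductions of 50–90%: from 20 000 × 0.005 × 0.10 = 10 cases to 20 000 × 0.02 × 0.50 = 200 cases. Deaths run from 10 × 0.068 = 0.7 to 200 × 0.105 = 21.

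Under the list, the 14–21 standard-care deaths are zero SAEs. The ciprofloxacin-arm figures are ceilings on post-dose events, because some cases arise before dosing, in non-recipients or after 28 days.

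**The case against.** The best defence of the causality section is to read it as a whole. An unrelated category, a list of confounders and a two-person adjudication make no sense if every post-dose event is related, so immediate events must have been intended. That is probably right. What stands against it is that the sentence will be applied as written, and one changed word would remove the doubt.

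On the definition, it is fair to say that the first version is not limited to ciprofloxacin and that surveillance explicitly covers everyone. It would therefore be wrong to say that the plan defines SAEs only in ciprofloxacin takers. The defect is two unreconciled definitions, the operative one of which does not match the population under watch. It is also fair that safety is not a listed objective and that the chapter is built for individual reporting. A by-arm table would add to the plan's purpose, but it uses surveillance the plan already claims to have.

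On meningitis, *Meningitis surveillance and incidence calculations* records village, outcome and ciprofloxacin receipt for each suspected case, and the SAE form records the type of event. Meningitis can therefore be separated afterwards and compared across arms. This leaves only a missing statement of how it will be handled.

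A reader might infer two stronger things. One is that the safety count would be dominated by meningitis. The documents do not show this: they give no admission rate and no background mortality. If crude mortality of 8–15 per 1 000 per year is assumed, with everyone dosed and every death captured, 28-day background deaths in 20 000 people would be 20 000 × 28/365 × 0.008 to 0.015, or about 12–23. That exceeds the 4–6 meningitis deaths in the example. The other inference is that a drug signal could not be told from background. Individual causality review, recorded cause of death and event type, and the meningitis data in all arms argue against so flat a statement.

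**Conclusion.** The point holds as a conflict between stated rules. Read literally, the automatic-relatedness sentence overrides the 28-day assessment. The operative SAE list also excludes standard-care residents and non-recipients whom the plan places under surveillance, so a randomized comparison of serious events is lost. The missing rule for endpoint meningitis is secondary.

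The conclusion rests on the wording alone. The case and death counts are illustrative and depend on the protocol's planning example. The effect is confined to safety classification and reporting, including the quarterly SAE report to the national ethics committee. The primary analysis and the sample size do not change. The passages should be reconciled before the first dose.

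**What to change.** 1. In *Assessment of causality*, limit the automatic rule to SAEs with onset inside the 30-minute window the sentence already names, stated as a limit and not an example. Leave all other SAEs to the 28-day assessment, and name the same assessors in both safety sections.
2. In *Documenting serious adverse events*, replace the two definitions with one event-capture definition that does not depend on having taken ciprofloxacin. Record ciprofloxacin receipt and date as attributes of the event.
3. In the written analytic plan, tabulate facility-recorded serious events by arm, per 1 000 residents, using the village census as denominator. Count them over a window anchored on each village's inclusion. A shared calendar window would not suit villages that enter at different times.
4. State that meningitis meeting the case definition is shown separately from other serious events, by arm.

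The first two items and the last are mainly wording. The third needs event forms for standard-care residents and non-recipients, a real workload when the protocol expects at least 60 000 subjects. Because surveillance is passive and facility-based, capture will be incomplete in every arm, and the table should be read as a comparison of facility-recorded events.

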**MONITORING**

The sponsor will permit trial-related monitoring and Institutional Review Board review, providing direct access to source data and documents.

A qualified and appropriately-trained Study Monitor will be designated by the sponsor to carefully monitor all aspects of the study.

The Study Monitor will perform an initial audit before the start of the study to ensure all necessary tools and supports are in place for study implementation. During the project period, the Study Monitor will routinely contact study sites and perform on-site visits to inspect facilities and documentation, observe performance of study procedures, discuss the protocol in detail and identify and clarify any areas of weakness. The extent, nature and frequency of site visits during the project period will be based on considerations of study objectives, study design and complexity, and enrollment rate.

Monitoring will be conducted according to good practice guidelines and study SOPs. The Study Monitor will have access to all records necessary to ensure the integrity/validity of the recorded data and will periodically review the progress of the study. During site visits and contacts, the Study Monitor will specifically:

1. Check and assess the progress of the study

2. Review study data collected

3. Perform source data verification to verify compliance with study SOPs

4. Verify compliance with human subjects protection and research guidelines

5. Identify any issues and discuss possibilities to address their resolution with the Sponsor and Field Investigator

This will be done in order to verify that:

1. The data are authentic, accurate and complete

2. The safety and rights of participants are being protected

3. The study is conducted in accordance with the approved protocol (and any subsequent amendment), and all applicable administrative requirements

**ETHICAL CONSIDERATIONS**

**Ethical considerations particular to cluster-randomized trials**

A variety of ethical questions should be considered when designing and implementing cluster-randomized trials. These questions include who is considered a research subject; from whom, how and when informed consent should be obtained; whether clinical equipoise exists; the determination of risks and benefits; the protection of vulnerable groups; and the roles and responsibilities of “gatekeepers” (Weijer, 2011).

A series of recommendations for the ethical design and conduct of cluster randomized trials was developed by a consensus group in 2012, referred to as the Ottawa Statement (Weijer, 2012). Several flaws have been identified in the original statement, particularly regarding the definition of study subjects and the disclosure of randomization (van der Graaf, 2015).

The literature surrounding the ethical considerations of cluster-randomized trials is biased towards developed-country settings. The conduct of such trials in sub-Saharan Africa is less well-represented in the literature. This is important both because the setting and contexts are different, but also because the types of intervention are often quite different from those seen in the developed world. One recent description from a cluster-randomized trial carried out in schools in Kenya describes a number of logistical and ethical difficulties, particularly regarding community involvement and informed consent (Okello, 2013).

The setting of the proposed cluster-randomized trial poses some challenges. Conducting research during an emergency such as a meningitis outbreak is challenging, particularly given the fear that a meningitis outbreak can provoke in the population.

Two general types of cluster-randomized trials have been described (Sim, 2012). The first is a “cluster-cluster” trial, where the intervention necessarily takes place at the cluster level (such as treatment of a community well). The second is an “individual-cluster”, where the intervention takes places at the individual or household level. The proposed trial is an “individual-cluster” trial in the paradigm described by Sim, which necessitates the special consideration of the role of political and administrative authorities as gatekeepers, as well as the nature of individual consent for participation.

The following sections will address some of the important ethical considerations of the proposed trial design, taking into account the guidance of the Ottawa Statement and other important documents from the medical/ethical literature on the subject of cluster-randomized trials.

**Summary of known and potential risks, identification of vulnerable populations**

There is no data on the use of ciprofloxacin as an epidemic response in the meningitis belt of sub-Saharan Africa. However, based on documentation of safety of its use in multiple other settings, the individual risks associated with its use as a single-dose prophylactic treatment in this trial are expected to be minimal, including among pregnant women and children, as described above.

One potential community-level risk associated with the use of ciprofloxacin as prophylaxis is the development of enterobacteriaceae resistant to fluoroquinolones. In the event of a positive primary outcome, no recommendation on the routine use of ciprofloxacin in similar settings would be given without a description of the potential effects of the strategy on antibiotic resistance. The resistance sub-study seeks to respond to this open question and quantify the risk, if any, associated with single-dose ciprofloxacin.

All clinical procedures (administration of ciprofloxacin and preparation of stool samples) will be performed by adequately trained and experienced personnel under regular supervision to minimize any risk or discomfort to participants. Resistance sub-study participants may have a higher risk of fecal-oral contamination. To combat this risk, sub-study participants will be provided soap before each sample collection and instructions on handwashing after defecation and sample collection.

Given the difficult-to-predict evolution of meningitis epidemics, it is also possible that the study would not reach its target sample size, and therefore not have sufficient power to evaluate the primary outcome. This could happen because the epidemic naturally does not reach a large enough magnitude, or because a reactive vaccination campaign is undertaken in some or part of the study area. No reactive vaccination will be stopped or delayed due to the implementation of this study.

**Risk minimization and benefits**

All personnel involved in collecting and processing biological samples are trained health care personnel, who will be provided with additional training to avoid or minimize the possibility of any unplanned side effects of these procedures.

The direct benefits individual participants may expect from participating in this study include receiving information about the signs and symptoms of meningitis and information about the free nature of health care during such an epidemic. All participants may also expect to benefit from contacts with members of the study team and the assurance of the best available medical care with close and regular surveillance. Recipients of ciprofloxacin may also potentially benefit from the possible protective effect of the antibiotic against the subsequent development of meningitis. At the population level, an important benefit of obtaining data on the efficacy of the use of ciprofloxacin in response to an epidemic, if proven protective, is the antibiotic potentially being made available for a larger population, particularly in light of current shortages of vaccine against NmC.

To minimize the risk of not reaching the target sample size, starting criteria have been set forth to reduce the possibility of starting the trial too early in an epidemic. Given that reactive vaccination remains the recommended epidemic response for meningitis, all study areas would be evaluated for reactive vaccination by the local health authorities following the usual procedures in place in Niger, and would be eligible for reactive vaccination campaigns. Nonetheless, reactive vaccination campaigns often take 6-8 weeks to organize, so if the proposed study is put into place early in the epidemic, the amount of study inclusion time without this potential confounding factor will be maximized.

**Definition of research subject and identification of gatekeepers**

Given that the primary outcome of interest is the overall meningitis incidence in the three different arms, all residents of randomized villages should be considered research subjects (Weijer, 2012; van der Graaf, 2015). Although there are certain unknowns regarding the sample size necessary for the evaluation of the primary outcome (see section “Sample Size” above), even when using conservative estimates, we could reasonably expect at least 20 000 persons to be living in the study area of each arm, therefore a total of at least 60 000 research subjects under the current definition.

The logical “gatekeepers” as described by the Ottawa Statement for the proposed trial are the health and political/administrative leaders of the study areas in question. For the purposes of this study, the gatekeepers who will be asked for permission will be the doctor or nurse in charge of the Health Center in a given HA, as well as the village chief and his/her deputies for the villages eligible for inclusion.

**Informed consent**

The role of gatekeepers in the proposed trial is extremely important, but their permission for participation in the trial will not be considered proxy consent for an individual’s participation in the trial (Weijer, 2012). Nonetheless, following the Ottawa Statement, given that the proposed trial would substantially affect the interests of the cluster (village, HA), we will obtain the permission of the identified gatekeepers in each HA and village eligible for inclusion in the trial. This permission will be documented following the traditional format of an informed consent procedure for inclusion in a study. The process of obtaining permission for randomization will consist of the explanation and discussion of an informational notice (Appendix A) about the purpose of the study, the study interventions, procedures to be followed and the risks and benefits of participation, both for the HA/village as a whole and for individual participants. The informational notice, the discussion and written permission document will be reproduced in the local language. At the village level, at the end of this process, the village chief will be asked to sign the permission document for the village.

In the arms which will receive ciprofloxacin distribution (either village-wide or household-level) it will not be possible to obtain written informed consent from each individual who receives ciprofloxacin. As described above, it is likely that over 20 000 people will be included in the village-wide prophylaxis arm, and in the household-level prophylaxis arm, several thousands are also likely to be eligible to receive ciprofloxacin. In the setting of a public health emergency, obtaining written informed consent from each participant is simply logistically impossible.

As detailed by Sim, written informed consent of each participant in a cluster-randomized trial should not be considered an absolute requirement (Sim, 2012), and the context of the proposed trial meets the conditions set out for this. The waiver of individual-level consent is also foreseen in the Ottawa Statement (Weijer, 2012). Nonetheless, as pointed out by Sim, “Although informed consent may not be sought in a cluster-randomized trial, the goals that it seeks to achieve may nonetheless by protected by other means.”

Therefore, in villages randomized to household-level prophylaxis, when the study nurse visits an eligible household, he or she will present the study, its interventions, procedures to be followed and the risks and benefits of participation following the text presented in the informational notice for participants (Appendix B). The members of the household will be given opportunity to ask questions and only those willing to take ciprofloxacin will be administered the drug.

In villages randomized to village-wide prophylaxis, a series of community informational sessions will be organized in advance of the distribution. A text (Appendix B) that presents the study, its interventions, the procedures to be followed, the voluntary nature of participation and the risks and benefits of participation will be read during this meeting, and community members will be given the opportunity to ask questions. The logistical setup of these informational sessions will vary depending on village size and other factors, but the goal will be to have one session for each 25 households, as to allow for better participation. Similarly, during the sensitization campaigns prior to the distribution, the voluntary nature of participation will be underlined. Those people who present to the distribution site will therefore be considered to have been duly informed of the risks and benefits of their taking ciprofloxacin and the voluntary nature of their participation.

The plan outlined in the above two paragraphs is in line with the Ottawa Statement and the criteria set out by Sim.

Written informed consent will be sought prior to inclusion in the resistance substudy. Prior to collection of the first sample, the study nurse will read aloud in the local language the informational notice and informed consent form for the substudy (Appendix C). This informational notice will include information on the purpose of the sub-study, procedures to be followed and the risks and benefits of participation. Study staff will give the participant or their parent/guardian ample opportunity to inquire about details of the study and ask any questions. The notice will be read to the participant in the presence of a literate and impartial witness. The witness will sign and date the consent form to attest the consent process appears to be fair and the participant (or their parent/guardian) voluntarily accepts to participate.

One copy of the Informed Consent Form will be kept on file by the Field Investigator. The participant will receive the Information Sheet and a second copy of the signed and dated Informed Consent Form.

